### Decision rule

A single sufficient decision rule will be taken to interpret the results: the primary endpoint will be considered to be reached if at least one dimension among the two targeted ones (physical and cognitive fatigue) will be statistically significant in favour of the intervention arm, in absence of a statistically significant negative result on the other dimension.

For secondary endpoints, data at randomization will be compared between the 2 arms, and then the absolute and relative variations between inclusion and the different measurement times will be described and compared by arm. Longitudinal analysis of HRQoL will be performed by including all available measurement time until Y3. A mixed model for repeated measures will be performed including the randomized group, time, and intervention by time interaction, as well as random effect on intercept and time to reflect the individual deviance at baseline and over time. The proportion of patients with stable, deteriorated, and improved HRQoL using the MID at M12, and at Y3. Each HRQoL score from the EORTC questionnaire will be analysed. The MID will be fixed to 10 points for each HRQoL score of the EORTC questionnaires. Time to improvement or deterioration of HRQoL could also be proposed in complement using Kaplan-Meier survival estimation [58, 59]. A detailed statistical analysis plan will be written for each endpoint before the data is frozen.

For the gut microbiota study, to investigate whether the gut microbiota and its metabolites mediate the positive effect of PA on CRF and other short- and long-term sequelae in metastatic TGCT patients receiving chemotherapy, we will apply two steps of statistical analyses overall: Step 1 to test “the impact of PA on the chemotherapy-induced alterations in the gut microbiota and relevant metabolites” and Step 2 to test “the effect of the gut microbiota and relevant metabolites modulated by PA on CRF and other short- and long-term sequelae in metastatic TGCT patients receiving chemotherapy”.

To identify discriminated taxonomic features between the two arms at different taxonomic levels, we will apply the DESeq test (The R “DESeq” package) [60] corrected for multi-comparisons using the Benjamini–Hochberg procedure [61]. Then, we will conduct partial Spearman correlation analyses among identified taxonomic features, CRF and other sequelae scores, and levels of inflammation/immunity biomarkers. Prior to analysis, the taxonomic composition data will be centred log-ratio transformed for handling zeros in the dataset based on a Bayesian-multiplicative replacement according to a guideline for compositional analysis of omics-data [62].

To examine the difference in the diversity and metabolites of the gut microbiota between the two arms and its association with CRF and other sequelae scores and levels of inflammation/immunity, we will apply general linear models (GLMs) for α-diversity and gut microbial metabolites (e.g., SCFAs, bile acids, GABA, tryptophan metabolites) and permutational multivariate analysis of variance (PERMANOVA) and principal coordinate analysis (PCoA) for β-diversity.

In addition, to explore trajectories of composition, diversity and metabolites of the gut microbiota along with chemotherapy and PA intervention, we will use linear/non-linear mixed effect models (The R “TcGSA” package) [63], using the cubic function for time modelling.

All models applied in this study will be adjusted for factors associated with PA performance, the gut microbiota, and sequelae of TGCT patients using a Directed Acyclic Graph (e.g., age, BMI, body composition, other lifestyle factors– diet, smoking, alcohol intake, socioeconomic factors, initial psychological disorders, etc.).

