### Recruitment

Participants will be recruited from several comprehensive cancer centres, hospitals, and clinics in France. After a systematic screening through patient files and/or the weekly multidisciplinary testicular cancer board, the study will be proposed to eligible patients by the investigator, with the support of a clinical research assistant. During the chemotherapy consultation, the investigators will check the eligibility criteria, deliver the study information sheet, and explain the objectives and the procedure to eligible patients. The patients will be given sufficient time for reflection, and the investigators will answer their questions if necessary. Patients who agree to participate will give informed consent, by means of a dated and signed informed consent form. A copy of the consent signed jointly by the investigator will be given to the patient. At the same time, the investigator, after a clinical examination, will issue a medical certificate of no contraindication to practice PA. The inclusion of patients is possible until the 3rd day of the first cycle of the first line of chemotherapy. The number of eligible patients who refuse to participate will be recorded in a screening dashboard.

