### Statistical analysis

All statistical analyses will be performed using the R statistical software (ver. 4.3.0, R Development Core Team, 2023) and SAS (ver. 9.4, The SAS Institute, Cary, NC, USA).

Categorical variables will be described using frequency distributions and percentages. The number of missing data will be indicated, but will not be taken into account for the calculations. Quantitative data will be described using the number of observations, mean, standard deviation, median, minimum and maximum values. The date of randomization will be considered as the reference date in all time calculations unless otherwise specified. An ITT analysis will be used to avoid attrition bias. Data at inclusion will be described in the ITT population and presented by the randomization arm. Results will be considered significant when the *p*-value is less than or equal to 0.05, except for the primary endpoint (alpha set at 0.025).

For the primary endpoint, the minimal important difference (MID) will be set to 10 points for each fatigue score (physical and cognitive) (MID = 0.5*SD) [56, 57]. These dimensions of the EORTC QLQ-FA12 will be analysed at 3 years. A Student-t test will be used to compare the scores between the two arms at 3 years, adjusting for the level of HRQoL at inclusion. In case of non-normal distribution, a non-parametric Mann-Whitney test will be performed. An analysis of the missing data profile at baseline and during follow-up will be performed to determine the missing data profile. An effort will be made to have all patients complete the baseline questionnaire as well as the 3-year questionnaire, to ensure the statistical power for the primary analysis. Stratified analyses will be performed according to stratification criteria of the randomisation.

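### Secondary endpoints are compared on change from D0 with no D0 covariate named, and D0 itself is compared between arms; a D0 covariate would recover (1-r)/2 of the information

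*Protocol article*

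**What the plan says.** The rule for secondary endpoints is in the protocol article under *Decision rule*. It has two steps. First, "data at randomization will be compared between the 2 arms". Then "the absolute and relative variations between inclusion and the different measurement times will be described and compared by arm". No test, model or baseline covariate is named for either step.

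Three other statements bear on this:

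- *Statistical analysis* handles baseline data descriptively: "Data at inclusion will be described in the ITT population and presented by the randomization arm".
- The same section does use a baseline level in the primary comparison. The test is to "compare the scores between the two arms at 3 years, adjusting for the level of HRQoL at inclusion".
- *Decision rule* gives HRQoL its own longitudinal analysis: "A mixed model for repeated measures will be performed including the randomized group, time, and intervention by time interaction". No such model is stated for the other secondary endpoints.

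The D0 assessment falls around the start of treatment: "The inclusion of patients is possible until the 3rd day of the first cycle of the first line of chemotherapy".

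**The concern.** Allocation is randomized, so the arms differ at D0 only by chance and a formal comparison there answers no useful question. The general significance rule (a p-value that "is less than or equal to 0.05, except for the primary endpoint (alpha set at 0.025") has no exception for baseline data. If tests were run under it, about 5% of D0 variables would be flagged by chance alone.

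The second step costs more. Subtracting D0 removes what D0 predicts about the later score, but it also adds all of D0's own variability. If D0 and follow-up are only modestly correlated, the subtraction adds more noise than it removes. Using D0 as a covariate weights it by how well it predicts the later score. At stake is the precision of endpoints such as HADS, FACT-Cog, the 6-minute walk, sit-to-stand, handgrip, anthropometry and biomarkers, all of which have a D0 value under *Data/biospecimen collection*.

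**Working it through.** **The plan's own figure.** The article states no precision for secondary endpoints, but its primary sample size gives a frame. *Sample size* has a difference of 10, SD 20, two-sided alpha 0.025 and power 90%. Per arm, n = 2 × 20² × (2.241 + 1.282)² / 10² = 99.3, so 100 per arm and 200 evaluable. Allowing for 15% loss, 200 / 0.85 = 235.3, which rounds up to 236, or 118 per arm. The figure reproduces.

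**Inputs for the check.** 100 evaluable per arm comes from *Sample size*. Alpha 0.05 for secondary endpoints comes from *Statistical analysis*; two-sided is assumed. The correlation r between D0 and follow-up is not given anywhere, so the range 0 to 0.9 is shown. Equal SDs at D0 and follow-up are assumed first, then relaxed.

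**Variance relative to the follow-up score alone (equal SDs).**

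- Follow-up score alone: 1
- Absolute change: 2(1-r)
- Follow-up score with D0 covariate: 1-r²

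The information lost by change against the covariate analysis is 1 - (1-r²)/[2(1-r)] = 1 - (1+r)/2 = (1-r)/2. Change has a larger variance than the follow-up score alone when 2(1-r) > 1, that is, r < 0.5.

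The power columns use a 7-point difference and SD 20 at both times, 100 per arm, two-sided 0.05. The 7 points are illustrative, and SD 20 is the plan's fatigue value, used here only as a scale. Power = Φ(7 / [20 × √(2v/100)] - 1.96), where v is the variance factor above.

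| r | Variance, change | Variance, D0 covariate | Information lost by change | Power, change | Power, follow-up alone | Power, D0 covariate |
|---|---|---|---|---|---|---|
| 0 | 2.0 | 1.00 | 50% | 41.7% | 69.7% | 69.7% |
| 0.2 | 1.6 | 0.96 | 40% | 49.9% | 69.7% | 71.4% |
| 0.3 | 1.4 | 0.91 | 35% | 55.2% | 69.7% | 73.7% |
| 0.5 | 1.0 | 0.75 | 25% | 69.7% | 69.7% | 81.5% |
| 0.7 | 0.6 | 0.51 | 15% | 89.2% | 69.7% | 93.4% |
| 0.8 | 0.4 | 0.36 | 10% | 97.5% | 69.7% | 98.5% |
| 0.9 | 0.2 | 0.19 | 5% | 100% | 69.7% | 100% |

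A simulation with 100 per arm gave losses of 39.8%, 25.6% and 9.3% at r = 0.2, 0.5 and 0.8, in line with the formula.

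**Unequal SDs.** Let k be the D0 SD divided by the follow-up SD. The variance of change is then 1 + k² - 2rk, and the break-even r is k/2. With k = 0.75 the break-even is 0.375, and the loss over r = 0.2 to 0.5 runs from 24% to 8%. With k = 1.25 the break-even is 0.625, and the loss runs from 54% to 43%.

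**Chance imbalance.** With equal SDs, if the arms happen to differ by d at D0, the expected difference in change is shifted by rd - d = -(1-r)d. At SD 20 and 100 per arm, the standard error of the D0 difference is 20 × √(2/100) = 2.83 points. An imbalance of that size at r = 0.3 shifts the change comparison by 0.7 × 2.83 = 2.0 points. The covariate analysis removes this shift. Over all randomizations the shifts average to zero.

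**The case against.** The strongest reply is that the article does not call the change comparison unadjusted. It promises a detailed analysis plan for each endpoint, and covariates are often left to that plan. Change analysed with D0 as covariate also gives the same arm effect and standard error as the follow-up score with D0 as covariate, so the wording is compatible with the fix. This stands in part: the defect is a stated comparison with no baseline term named, not a stated refusal to adjust. But the article fixes change from inclusion as the quantity compared, and an analysis plan that follows it literally would inherit the loss.

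A second reply points to the sentence closing the gut-microbiota methods, which says all models in the study will be adjusted for factors such as BMI, body composition and initial psychological disorders. Read literally, it could reach anthropometry and, less directly, HADS. Its position suggests a narrower scope, and it does not make each outcome's own D0 value a general covariate.

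Third, HRQoL has a mixed model. That is why the point is confined to endpoints with no other stated model.

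A reader might also draw stronger conclusions than the documents support:

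- **That 25 to 40% of the information is lost and change is likely noisier than ignoring D0.** This needs r between 0.2 and 0.5 with equal SDs, neither of which is given; at r = 0.5 the two are equally noisy. A low r at Y3 is plausible for symptom scores, because D0 falls at chemotherapy start. It is less plausible for weight or handgrip.
- **That D0 data will be tested.** The text says compared. Because the next clause separates describing from comparing, a test is a natural reading, but it is an inference.
- **That the change comparison is biased.** Under randomization it is unbiased overall.

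**Conclusion.** The point holds as a matter of efficiency. The between-arm comparison at randomization adds nothing to the description by arm already planned. For continuous secondary endpoints with a D0 value and no other stated model, comparing unadjusted change loses (1-r)/2 of the information a D0 covariate would keep. That is 50% at r = 0, 25% at r = 0.5 and 5% at r = 0.9, assuming equal SDs, and it moves either way if the SDs differ. With equal SDs, change is noisier than discarding D0 altogether only for r below 0.5. The exact loss for any endpoint cannot be stated from the documents, but in large samples the covariate analysis is never less precise, whatever r is.

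Endpoints without a D0 value (return to work, relapse, cardiovascular toxicity, second cancers) are outside the point. The primary analysis, its decision rule and the sample size are unaffected. The change is worth making because D0 is already collected for these endpoints.

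**What to change.** In *Decision rule*:

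1. Remove the between-arm comparison of data at randomization and rely on the description by arm already given in *Statistical analysis*, without p-values.
2. For each continuous secondary endpoint with a D0 value, compare the arms on the score at each visit with that endpoint's own D0 score as covariate.
3. Report absolute change from D0 by arm descriptively only. Relative change should not be a basis for comparison: a score such as a HADS subscale can be 0 at D0, which leaves the percentage undefined.

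The cost is wording in the protocol and the analysis plan, made before the data are frozen. No new data, visits or patients are needed.

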### Study objectives

Objective 1: to investigate the impact of a one-year supervised PA program implemented concomitantly with first-line cisplatin-based chemotherapy, on CRF (primary outcome, both physical and cognitive aspects of CRF at 3 years) and other short- and long-term sequelae (secondary outcomes: another dimension of CRF– emotional fatigue, HRQoL, cognition, anxiety/depression, anthropometry, physical condition, PA/sedentary behaviour level, pain and neuropathy, sustainable return to work, sleep quality, heart rate, TGCT relapse, cardiovascular toxicities, secondary primary malignancy, immune/inflammatory/liver function biomarkers) in first-line metastatic TGCT patients (Hypothesis 1).

Objective 2: to investigate how the gut microbiota (diversity and taxonomic composition) and its metabolites involved in the gut-brain axis (e.g., SCFAs, bile acids, GABA, tryptophan metabolites including serotonin) mediate the impact of PA on primary and secondary outcomes in metastatic TGCT patients receiving chemotherapy (Hypothesis 2).

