## Statistical considerations

### Sample size

In order to evaluate our primary endpoint and to detect a minimum significant difference ≥ 10 points in the CRF scores between the 2 groups at 3 years, with a standard deviation of 20, considering 2 dimensions of CRF (physical and cognitive fatigue) assessed by the EORTC QLQ-FA12 questionnaire, with a bilateral alpha, type I error of 0.025 (Bonferroni adjusted *p*-value for two targeted dimensions, overall risk of 5%), a statistical power of 90%, 200 patients with fatigue scores available at baseline and 3 years is required. Considering 15% of lost to follow-up or unavailable data and patients without fatigue scores available, 118 patients per group will be randomized (1:1), for a total of 236 patients.

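### The mediation objective is assigned a two-step analysis in which no named method estimates or tests an indirect effect, and conditioning on randomised arm and time order are left unstated

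*Protocol article*

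**What the plan says.** Mediation is in the title, in the second study hypothesis and in Objective 2, which asks how the microbiota and its metabolites "mediate the impact of PA on primary and secondary outcomes in metastatic TGCT patients receiving chemotherapy" (protocol article, Study objectives).

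The analysis is set out under Statistical considerations, within the Decision rule section. Its stated purpose is "to investigate whether the gut microbiota and its metabolites mediate the positive effect of PA on CRF" and the other sequelae. Step 1 tests the effect of physical activity on the microbiota and metabolites. Step 2 tests the effect of the microbiota and metabolites on fatigue and the sequelae.

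The methods are named:
- **Taxa, step 1:** DESeq between arms, with Benjamini–Hochberg correction.
- **Taxa, step 2:** "Then, we will conduct partial Spearman correlation analyses among identified taxonomic features, CRF and other sequelae scores, and levels of inflammation/immunity biomarkers".
- **Alpha-diversity and metabolites:** general linear models, for both the arm difference and the association with outcomes.
- **Beta-diversity:** PERMANOVA and principal coordinate analysis.
- **Trajectories:** linear or non-linear mixed models with a cubic function of time.

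On adjustment: "All models applied in this study will be adjusted for factors associated with PA performance, the gut microbiota, and sequelae of TGCT patients", chosen with a directed acyclic graph. The examples are age, BMI, body composition, lifestyle and socioeconomic factors and initial psychological disorders, and the list is left open.

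Microbiota and metabolites are measured at D0, end of chemotherapy (M3), M12 and Y3. The primary fatigue outcome is at Y3. Faecal sampling is optional.

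**The concern.** A mediation claim needs three things: an effect of arm on the mediator, an effect of the mediator on the outcome among patients of the same arm, and a mediator measured before the outcome. An estimate also needs the first two combined into an indirect effect with an interval. The plan has the first. For the second it names association methods without saying that arm is held fixed. It does not fix the third, so a correlation of Y3 microbiota with Y3 fatigue would comply. Nothing in it combines the two paths.

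The selection in step 1 makes this sharper. Taxa go forward because they differ by arm. If physical activity also lowers fatigue, as the trial hypothesises, such taxa are associated with fatigue even where neither affects the other. A title-level aim could then be reported as supported by a by-product of randomisation. Even a sound positive result would give no size for the mediated effect.

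**Working it through.** **1. The plan's own figures.** The inputs from the Sample size section are a "minimum significant difference ≥ 10 points in the CRF scores between the 2 groups at 3 years", "with a standard deviation of 20", "with a bilateral alpha, type I error of 0.025" for each fatigue dimension, and "a statistical power of 90" per cent.

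n per arm = 2 × (z₀.₉₈₇₅ + z₀.₉₀)² × (SD/difference)² = 2 × (2.241 + 1.282)² × (20/10)² ≈ 99.3, so 100 per arm and 200 in total. With 15% loss, 200/0.85 = 235.3, so 236. Power at 100 per arm is 90.2%. The stated sample size is reproduced and is not in dispute. It also supplies the standardised outcome effect used below, 10/20 = 0.5 SD. No sample size, power or effect size is given for the mediation objective.

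**2. Objective against methods.**

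| What mediation needs | What the plan names |
|---|---|
| Arm to mediator | DESeq, linear models, PERMANOVA between arms |
| Mediator to outcome, given arm | Partial Spearman and linear models; arm not named among the conditioning variables |
| Mediator before outcome | Visits listed, pairing not stated |
| Indirect effect with interval | Nothing |

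**3. What follows if arm is left out of step 2.** Let A be arm (0/1, equal groups), M = aA + e₁ and Y = cA + e₂, with independent standard normal errors. There is no path from M to Y, so no mediation. The correlation of M and Y pooled over arms has absolute size

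|a| × |c| × 0.25 / √[(1 + a²/4)(1 + c²/4)].

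With |c| = 0.5 this is 0.059, 0.090 and 0.108 for a = 0.5, 0.8 and 1.0. It arises wholly from arm.

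In simulation (4,000 trials per setting, rank correlation, two-sided 5%), the rejection rates were:

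| N | Taxon shift a (SD) | Arm not conditioned on | Same, among taxa significant by arm | Arm partialled out |
|---|---|---|---|---|
| 100 | 0.5 | 8.6% | 9.8% | 5.3% |
| 100 | 0.8 | 15.0% | 15.3% | 5.4% |
| 100 | 1.0 | 19.0% | 19.0% | 5.2% |
| 200 | 0.5 | 12.7% | 13.2% | 5.2% |
| 200 | 0.8 | 23.8% | 23.8% | 5.0% |
| 200 | 1.0 | 33.2% | 33.2% | 5.6% |

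The fourth column uses a t-test as a stand-in for DESeq selection. The taxon shifts and both values of N are assumptions, since the article gives neither. N = 200 is the evaluable number for the primary endpoint and N = 100 a smaller optional sub-study.

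**4. What follows if arm is included.** The rejection rate returns to about 5%. Steps 1 and 2 together then amount to a joint-significance test of the two paths. That is evidence on mediation, but it still gives no estimate of the indirect effect.

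**The case against.** The strongest reply is that the plan may already condition on arm. The Spearman correlation is a partial one, its conditioning variables are not listed, and all models use a graph-derived adjustment set introduced by examples and left open. In a graph for the second hypothesis, arm is a common cause of microbiota and fatigue, so the usual rules would put it in the step 2 set. Initial psychological disorders are among the examples, so baseline status is not ignored. This stands. A reader might infer that the plan omits arm from step 2 and therefore cannot show mediation. The text does not support that: it neither names arm nor excludes it. The inflated rates above are accordingly conditional on an omission that is not established.

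It is also fair that the plan is more than arm comparisons and correlations. Alpha-diversity and metabolites go through linear models, and trajectories through mixed models. Neither is described as yielding an indirect effect.

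Finally, the article is condensed, promises a detailed statistical analysis plan for each endpoint, and treats the microbiota study as optional and ancillary. Interaction terms or a bootstrap would ordinarily be left to that plan. This reply carries less weight for the main point. The article does not leave the mediation method open: it names tests, R packages, the multiplicity procedure, the data transformation and the time function, and offers them as the answer to the mediation question.

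**Conclusion.** The point holds as a mismatch between objective and stated analysis. Followed exactly, the plan would yield arm differences, associations and trajectories, but no indirect effect, no interval for one, and no guaranteed order in time. Whether step 2 is also open to spurious association depends on whether arm is in the conditioning set, which the article does not say.

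If arm is absent, the false-positive rate of a nominal 5% test is about 9–19% at N = 100 and 13–33% at N = 200. These ranges assume taxon shifts of 0.5 to 1.0 SD, a fatigue effect of 0.5 SD and no mediation. If arm is present, the rate is about 5%, and what remains is the missing estimate and the missing visit pairing. The point should be addressed because mediation is a headline aim. It does not touch the primary endpoint or the sample size.

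**What to change.** 1. State that randomised arm, the D0 value of the mediator and the D0 FA12 score are in every step 2 model, alongside the baseline confounders from the graph.
2. Pre-state a short list of mediators, for example alpha-diversity, short-chain fatty acids, bile acids and tryptophan metabolites. Use the M12 value (M3 as second) with each primary FA12 dimension at Y3.
3. Fit a mediator model (arm, D0 mediator, D0 FA12, baseline confounders) and an outcome model (the same terms plus the mediator and the arm-by-mediator interaction). Report the indirect effect with a bootstrap interval.
4. Add a sensitivity analysis for unmeasured mediator–outcome confounding, which randomisation of arm does not remove.
5. Label the remaining taxon correlations exploratory and not evidence of mediation.

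The visits needed are already in the assessment schedule, so the cost is wording and programming. The downside is wide intervals in an optional sub-study, and probably a more modest conclusion. If the sponsor prefers not to do this, the alternative is to reword Objective 2 as exploratory association.

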#### Gut microbiota study outcome

This ancillary study will be optional so that it does not hinder patient participation. Patients will be offered to participate in the ancillary study at baseline.

*Gut microbiota* [Time points: D0, end CT (M3), M12, and Y3]: Gut microbial diversity and taxonomic composition will be measured using full-length 16 S rRNA gene amplicon sequencing on DNA extracted from faecal samples [49]. Faecal samples will be taken using a FIT kit (OC-Auto Sampling tubes, Eiken, Japan) which includes all the necessary equipment for collecting. The first faecal sample will be taken in the hospital at the start of chemotherapy. The other samples will be taken by the patient at home. This kit will be given to the patient during the visits. Once the sample has been taken, the patient must indicate the date and time of the sample on a questionnaire and use a stamped envelope to send the sample and the questionnaire to the University of Lyon 1, responsible for storing and analysing the data. The mailing should be done as soon as possible, ideally within 24 h of the collection. The faecal sample received by post should be frozen and stored at -80 °C before NDA extraction. Total DNA will be extracted from the faecal samples using the PowerFecal DNA Isolation kit (MoBio Laboratories, Carlsbad, CA, USA). DNA extracts will be stored at -20 °C before use. The 16 S rRNA V1-V9 gene will be amplified and sequenced using Oxford nanopore technology (3rd generation sequencing) [49]. The sequence data will be processed bioinformatically using a pipeline within QIIME2 [50, 51] to calculate (1) the relative abundance (%Amplicon Sequence Variant, ASV) of bacterial taxa, (2) within-sample (alpha-) diversity using the phylogenetic tree indices of Chao1, Shannon and Faith phylogenetic tree indices, and (3) between-sample (beta-) diversity using Bray-Curtis and unweighted and weighted UniFrac distance matrices.

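### The named arm comparisons for the gut microbiota do not state use of each patient's D0 sample, although Step 1 asks about alterations; adjusting for D0 would fit the question and add precision at no sampling cost

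*Protocol article*

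**What the plan says.** All of this is in the protocol article. The microbiota analysis stands at the end of the Decision rule section, under Statistical considerations.

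- **Question.** Step 1 is to test "the impact of PA on the chemotherapy-induced alterations in the gut microbiota and relevant metabolites".
- **Sampling.** The Gut microbiota study outcome section schedules stool at four visits: "Time points: D0, end CT (M3), M12, and Y3]: Gut microbial diversity". Serum for the metabolites follows the same schedule. Participation is optional, and no separate sample size is given.
- **Taxa.** "To identify discriminated taxonomic features between the two arms at different taxonomic levels, we will apply the DESeq test", "corrected for multi-comparisons using the Benjamini–Hochberg procedure". The taxa identified this way then enter partial Spearman correlations with fatigue, other sequelae and inflammation markers.
- **Diversity and metabolites.** The purpose is "To examine the difference in the diversity and metabolites of the gut microbiota between the two arms and its association with CRF" and other outcomes. The methods are: "we will apply general linear models (GLMs) for α-diversity and gut microbial metabolites", and "permutational multivariate analysis of variance (PERMANOVA) and principal coordinate analysis (PCoA) for β-diversity".
- **Trajectories.** Linear or non-linear mixed-effect models with a cubic time function are added, to explore trajectories of composition, diversity and metabolites.
- **Covariates.** All models are adjusted for factors chosen by a directed acyclic graph. The examples are age, BMI, body composition, lifestyle, socioeconomic factors and initial psychological disorders. The list is open-ended and does not name the D0 value of the microbiota variable.

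**The concern.** An alteration is a change from the patient's own state at D0. The three named tests are worded as differences between arms, with no visit, D0 value or contrast against D0. Elsewhere the same section is more specific: secondary endpoints get changes from inclusion compared by arm, and quality of life gets a repeated-measures model with an intervention-by-time term. The named microbiota comparisons get neither.

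The mixed models do not clearly fill this gap. They are introduced as an exploratory addition, and the text does not say whether they or the named tests answer Step 1. For taxa the order is explicit: DESeq identifies the features, and the correlations then use those features. The screen for the next step is therefore a test with no stated D0 term.

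At stake is precision. People differ in microbiota and metabolite levels before treatment. Without the D0 value, that stable variation stays in the error term, and real effects of the program are more easily missed. Taxa missed at this point do not reach the correlation analyses.

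**Working it through.** **1. The plan's own figure.** The only sample size in the document is for the primary fatigue endpoint. With a difference of 10, SD 20, two-sided alpha 0.025 and 90% power, n per arm = 2 × (2.241 + 1.282)² × (20/10)² = 99.3, so 100 per arm and 200 in total. Then 200/0.85 = 235.3, so 236. It reproduces, but it does not bear on the microbiota analysis, which has no stated power.

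**2. Inputs for the check.**
- From the document: D0 plus three follow-up visits (M3, M12, Y3), and a significance level of 0.05 outside the primary endpoint.
- Assumed: correlation rho between the D0 value and the follow-up value of the same variable, 0.5 with range 0.3 to 0.7; standardized arm difference d = 0.4; 100 or 50 contributing patients per arm.

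**3. One visit, D0 as covariate.** For a linear model the residual variance falls by the factor 1 − rho², which is 0.91, 0.75 and 0.51 at rho 0.3, 0.5 and 0.7. A comparison with 80% power has noncentrality 1.96 + 0.84 = 2.80. With the covariate this becomes 2.80/√(1 − rho²):

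| rho | noncentrality | power |
|---|---|---|
| no D0 term | 2.80 | 80% |
| 0.3 | 2.94 | 84% |
| 0.5 | 3.23 | 90% |
| 0.7 | 3.92 | 98% |

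**4. The same in terms of numbers, d = 0.4.**

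| per arm | no D0 term | rho 0.3 | rho 0.5 | rho 0.7 |
|---|---|---|---|---|
| 100 | 81% | 84% | 90% | 98% |
| 50 | 52% | 55% | 64% | 80% |

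The second row matters because participation is optional: 100 per arm would need 200 of 236 patients, or 85%, to contribute.

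**5. Simple change from D0.** The SD of a change score is √(2(1 − rho)) times that of a single value. At d = 0.4 and 100 per arm, power is 67%, 81% and 95% at rho 0.3, 0.5 and 0.7, against 81% with no D0 term. An unadjusted change score can therefore lose power when the correlation is low. The covariate form does not have this weakness.

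**6. Scope of the arithmetic.** These figures apply to approximately normal outcomes in a linear model, that is, alpha-diversity and suitably transformed metabolites. For DESeq and PERMANOVA the direction of the gain carries over, but its size was not calculated.

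**7. Error rate.** One visit per test means one sample per patient, and the error rate of a single test stays at 5%. Only if m visits were combined with no patient term would the variance be understated, by the factor 1 + (m − 1)rho. The true level would then be 2 × (1 − Φ(1.96/√(1 + (m − 1)rho))). At rho 0.3, 0.5 and 0.7 this is 12%, 17% and 21% for three visits, and 16%, 22% and 27% for four. Simulation with 100 per arm gave 13%, 16% and 21%, and 15%, 21% and 27%.

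**The case against.** The strongest reply is that most of this is silence in a condensed article. Visit, baseline term and permutation scheme are commonly left to an analysis plan, and the article announces a detailed one for each endpoint before data freeze. A general linear model can hold the D0 value as a covariate, PERMANOVA can be run per visit, and the covariate list is open. The mixed models cover the same three outcome families over a schedule that starts at D0. Most of this stands. It rules out saying that the plan excludes the D0 sample; it only does not state its use.

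A reader might go further and infer that the plan treats a patient's repeated samples as independent and so inflates its false-positive rate. The document does not support this. It nowhere says that visits are pooled, and a visit-by-visit comparison of randomized arms keeps its level. The 12% to 27% figures describe an analysis that nobody has stated. They also apply to a single unadjusted test, whereas the taxa tests are Benjamini–Hochberg corrected.

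Nor does the selection argument reach every outcome. Only taxa are explicitly carried forward from a test. For diversity and metabolites, one sentence covers both the arm difference and the association with outcomes, with no selection step.

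What remains is that the document does name specific tests, words them as arm differences while the question is about alterations, and makes one of them the screen for taxa.

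**Conclusion.** The point holds as a mismatch between question and named tests, with a cost in precision. Visit-by-visit comparisons would be valid. With D0 as covariate, 80% power would become about 90%, or 84% to 98% over the assumed correlations of 0.3 to 0.7. At d = 0.4 and 50 patients per arm, 52% would become 55% to 80%. The correlation, the effect size and the number of contributing patients are all assumptions, because the document gives none of them for this study.

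Inflated type I error is a risk to guard against in the wording, not a defect of the plan as written. The study is optional and ancillary, and the primary endpoint is not affected. The improvement is worthwhile mainly because the D0 samples are being collected anyway.

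**What to change.** In the microbiota part of the Decision rule section, or in the announced analysis plan before data freeze:

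- **Visit and role.** Name the follow-up visits (M3, M12, Y3) for each arm comparison, and say whether these tests or the mixed models decide Step 1.
- **Alpha-diversity and metabolites.** Fit a linear model per visit with the D0 value of the same variable as covariate. The alternative is one model over visits with an arm-by-visit contrast against D0 and a patient term.
- **Taxa.** Adjust for the D0 abundance of the same taxon, or test the arm-by-visit contrast against D0 with a patient term. Select the taxa for the correlation step from these D0-adjusted tests.
- **Beta-diversity.** Run PERMANOVA per visit or analyse the D0-to-visit distance. If visits are combined, permute whole patients.
- **Preference.** Use the covariate form where it is available, since an unadjusted change score loses power at low correlation.

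The cost is wording only, with no new samples. The small downside is that patients without a D0 sample need a missing-baseline rule, or they drop out of the adjusted comparison.
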